#### 2.6.2. Secondary Outcomes

The secondary outcomes will be measured immediately after completion of the whole intervention. The secondary outcomes are as follows: Opinion of the parents/guardians of the children in relation to the project: it will be completed by parents/guardians, online and without the presence of any member of the research group.Opinion of the children about the project reported by their parents/guardians: it will be completed by parents/guardians, online and without the presence of any member of the research group.

### 2.7. Data Management and Monitoring

Data will be stored in an anonymised form on corporate devices where only participating researchers will have access to credentials. All data provided for this research will be confidential as required by the European Data Protection Regulation [42] (EU2016/679). Data will be kept as long as their deletion is not requested by the person concerned and, in any case, as long as the periods of appeal and/or appropriate claim are open or as long as they continue to respond to the purpose for which they were obtained. The data controller is the University of the Basque Country (HN.GLUTEN3S, TI0233). 

### 2.8. Statistical Analysis

The description of the characteristics of the participants and data from the pre-, post- and retention test (one month after) questionnaires will be reported per group (control and intervention). 

For the analysis of the differences between groups, a variety of statistical tests will be used depending on the type of response to the questions (continuous, discrete or qualitative). Based on the distribution of the variables of interest in the sample, descriptive statistics for continuous data will be presented using the mean and standard deviation or the median and interquartile range. Qualitative data shall be presented as frequencies and percentages. Quantitative variables will be analysed using an ANOVA of repeated measures test using the group as a factor of the independent level (parametric) or Wilcoxon’s test segmenting by group (non-parametric). On the other hand, qualitative variables in two categories will be analysed with Chi-square and Cochran’s Q tests. Finally, qualitative variables in more than two categories will be analysed with Chi-square and McNemar Bowker’s tests.

Data will be entered and analysed using SPSS 28.0 software. A confidence interval of 95% and significance level of *p* < 0.05 will be assumed.

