## 2. Materials and Methods

### 2.1. Description

The Zeliakide project (the name comes from the union of two Basque words: “zeliako”, which means “celiac”, and “kide”, which means “companion”) is a one-month (4 weeks) intervention program, two-armed cluster, non-randomised and controlled trial, conducted among 10–12-year-old children with a pre- and post-intervention evaluation and 1 month follow-up to assess the effectiveness of the program.

The trial consists of a nutrition education intervention, focused on CD and the GFD. It is an intervention based on competencies and their respective learning outcomes. The teaching methodology chosen is inquiry-based learning (IBL). IBL enables children to acquire skills and knowledge through inquiry. It is a STEAM methodology that seeks to get children to ask questions, inspect, make measurements, design experiments, make logical reasoning based on evidence, and communicate the results.

The intervention is carried out by research experts in nutrition and CD, from the GLUTEN3S research team, and with experience in nutritional education activities. In addition, in order to highlight the role of women in science, they will be mainly women from this group who will go to the classroom to develop the intervention.

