### 2.3. Sample Size Calculation

Regarding knowledge acquisition, based on the results of a pilot experience of this program as well as other studies found in the bibliography, it has been estimated that to provide a power of 80% and an α error of 5% to detect a small–medium effect size (Cohen’s d of 0.32), 60 participants are required. Since detecting changes in attitude is more complicated, *n* = 120 participants will be proposed for such an outcome. Based in the dropout of similar studies [35,36,37], the final sample size will be increased by 20% to reach 144 children.

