### 2.4. Allocation to Groups

The distribution of the groups will be based on convenience as judged by experts (see the study flow in Figure 1). The intervention group will be made up of children whose teachers have communicated their wish to actively participate in the program. Teachers need to be involved in the intervention as they are aware of the situation in each classroom and it is necessary to carry out the activities correctly inside and outside the classroom.

As stated, the participants in the study will be students in the last cycle of primary education (10–12 years). The intervention will be carried out with pupils in the first year of this cycle (10–11 years) as, at this point, they acquire knowledge about nutrition and begin to develop scientific competence. All pupils in the same school, academic year and group should be part of the intervention group, since, from an ethical point of view, all groups should acquire the same knowledge during the school year. The control group will be formed by the students in the second year of the last cycle of the same primary school (11–12 years). 

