#### 2.5.2. Study Procedure

The study is schematically depicted in Figure 2. Data will be collected from participants before and after the intervention, using a specific questionnaire designed in order to evaluate the program (Appendix A Table A1). Due to the young age of the children, some limitations when reading and answering a questionnaire are expected, and so they will complete it in parts, thus avoiding the possible discomfort that a long questionnaire may generate in them. The pre-questionnaire part of each session will be completed at the beginning of the corresponding session and the post-questionnaire at the end of this session. They will have to complete a third questionnaire one month after the intervention in order to assess the maintenance of the acquired knowledge and behaviour. 

The pre- and post-intervention questionnaires will be completed with the help of 2–3 members of the research group, in addition to the school responsible teacher. They will help them to understand the questions they have to answer, always avoiding any influence. One month after the intervention, the post-questionnaire will be completed again with the help of the schoolteachers.

The control group will consist of a similar number of students to the intervention group; they will be part of the same school and their socio-demographic characteristics will be similar, even if they will be in the final year of the cycle. They will continue with the normal school curriculum. Students in the control group will be asked to complete a questionnaire as the intervention group, and they will have to answer it in the same month in which the intervention of the other group is being carried out. They will be helped by their teachers to understand the questions if necessary and will have to complete it in one session, since the aim is to avoid altering the usual routine of their classes.

Upon completion of the intervention, parents or guardians will be requested to fill out an online questionnaire to gather their feedback on the project as well as their children’s opinions, as reported by the parents.

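### The arms are whole classes or school years, but the between-arm tests treat children as independent and the sample size carries no allowance for clustering

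*Protocol article*

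**What the plan says.** - **Design.** Section 2.1 of the protocol article describes a "two-armed cluster, non-randomised and controlled trial".
- **Allocation.** Section 2.4 places intact groups in the intervention arm: "All pupils in the same school, academic year and group should be part of the intervention group". For the comparison, "The control group will be formed by the students in the second year of the last cycle of the same primary school". Section 2.5.2 adds: "The control group will consist of a similar number of students to the intervention group".
- **Delivery.** Sections 2.5.1 and 2.5.2 describe eight sessions taught to the class together, a month-long snack challenge scored by teams, and questionnaires completed with help from the research team or schoolteachers.
- **Sample size.** Section 2.3 works in individual children, at 80% power and a 5% α error: "Cohen’s d of 0.32), 60 participants are required". It proposes 120 for attitude without an effect size, then adds 20% for dropout to reach 144. It mentions no class size, number of classes, ICC or design effect.
- **Analysis.** Section 2.8: "Quantitative variables will be analysed using an ANOVA of repeated measures test using the group as a factor of the independent level (parametric"). The non-parametric alternative is a Wilcoxon test within each group. Categorical answers are tested by chi-square together with Cochran's Q or McNemar-Bowker. No class or school term, mixed model or cluster-robust error is named.
- **Limitations.** The Discussion names non-randomisation and the age difference between arms, but not clustering.

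**The concern.** Children taught together by the same people, in the same room and in the same competing teams are likely to change together. The comparison between arms then rests largely on the number of classes, while the child-level ANOVA and chi-square take their precision from the number of children. With positive correlation of change within class, the standard error of the arm effect is too small. The trial exists to judge whether the programme works, so an inflated false-positive rate bears directly on its main conclusion.

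This is not detail left to a fuller document. Section 2.8 names the tests, and the tests it names do not fit the design that section 2.1 declares.

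**Working it through.** **1. The plan's own figures.** The article does not name its formula. Two individual-level calculations come close to 60:

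- One-sample or paired test, one-sided 5%, 80% power: ((1.645 + 0.842)/0.32)² = 60.4, so 61.
- Repeated-measures ANOVA, between-group effect, with 0.32 entered as Cohen's f, two waves and an assumed correlation of 0.5: 60.

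The two-sided paired version gives 77. The last step is exact: 120 × 1.20 = 144. Neither calculation that comes close to 60 contains a cluster term, and the 20% is used up by dropout. That the sizing assumes independence is therefore an inference, but no figure points the other way.

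**2. Inputs that the article does not give.** Class size m = 20 to 24 and ICC of change = 0.01, 0.05 and 0.10 are assumptions.

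**3. Formulas.**

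- Design effect: DE = 1 + (m − 1) × ICC
- Effective number of children: 144/DE
- True type I error of a nominal two-sided 5% child-level test: 2 × [1 − Φ(1.96/√DE)]
- Reported interval width relative to the correct width: 1/√DE

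| m | ICC | DE | 144 is worth | Type I error | Relative width |
|---|---|---|---|---|---|
| 20 | 0.01 | 1 + 19 × 0.01 = 1.19 | 121 | 7.2% | 0.92 |
| 20 | 0.05 | 1.95 | 74 | 16.0% | 0.72 |
| 20 | 0.10 | 2.90 | 50 | 25.0% | 0.59 |
| 24 | 0.01 | 1 + 23 × 0.01 = 1.23 | 117 | 7.7% | 0.90 |
| 24 | 0.05 | 2.15 | 67 | 18.1% | 0.68 |
| 24 | 0.10 | 3.30 | 44 | 28.1% | 0.55 |

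**4. Check by simulation.** A child-level t-test on change scores, with three classes of 20 per arm, no true effect and 20,000 runs, rejected in 5.0%, 7.2%, 16.1% and 25.8% of runs at ICC 0, 0.01, 0.05 and 0.10. A paired comparison of class mean changes stayed at about 5% throughout.

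**5. Why a class random intercept alone is not enough.** The effect of interest is group × time. A class intercept is the same at every wave, so it cancels from each child's change. Take a change variance of 1 and 60 children per arm. The standard error of group × time is then √(2/60) = 0.183, whatever the variance of the class intercept, and this equals that of the child-level change test. With an ICC of change of 0.05 and m = 20, the correct value is √(2 × 1.95/60) = 0.255. Only a term for class variation in change captures the difference.

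**6. Detectable effect (illustration).** Take 120 analysed children in two equal arms, in SDs of the analysed score. The detectable d is 2.8 × √(4 × DE/120). It is 0.51 with no clustering, 0.56–0.57 at ICC 0.01, 0.71–0.75 at 0.05 and 0.87–0.93 at 0.10. These are large-sample values, and few classes make them worse.

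**The case against.** - **Shared schools and change scores reduce the problem.** Both arms come from the same schools, which removes part of the school-level correlation. Stable class differences cancel in pre–post change, and one research team delivers all intervention sessions. This stands, and it may keep the ICC near the low end. It does not make the ICC zero, because learning takes place by class. The cancellation also does not apply to a chi-square that compares the arms at a single wave.
- **The ICC is unknown.** True. That limits the statement of size. The direction holds for any positive ICC of change.
- **Some of the named tests do not compare arms.** Wilcoxon within group, Cochran's Q and McNemar-Bowker are within-arm tests. Clustering affects them as well, but the point here rests on the ANOVA and the between-arm chi-square.
- **Stronger readings.** A reader might infer that the effective sample is far below 144 in any case. The article does not support that: at ICC 0.01 it is still about 117–121. A reader might also see a conflict between the 20% increase for losses and an ANOVA that needs every wave. There is none, since such an increase is consistent with an analysis of completers.

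**Conclusion.** The point holds. The article declares a cluster design, fixes child-level between-arm tests, and sizes the study with no visible cluster term. If change correlates within class, p-values will be too small and intervals too narrow.

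The size is conditional on the assumed 20 to 24 children per class. The inflation is mild at an ICC of 0.01. At 0.05 the type I error is more than three times the nominal 5%, and at 0.10 it is at least five times. Confidence is high in the direction and limited in the magnitude.

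The detectable d of 0.51 without clustering already exceeds the 0.32 of section 2.3. A reader might put that gap down to clustering, but it is a separate matter of how the two-arm comparison was sized.

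**What to change.** **Section 2.8.** Make the main between-arm analysis one that carries class-level variation in change. Either of these would do:

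1. a class-level comparison of mean change between the 5th- and 6th-grade classes within school; or
2. a mixed model with a random class × time term (not only a class intercept), a random child intercept, school as a fixed effect, and Satterthwaite or Kenward-Roger degrees of freedom.

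For binary items, use the class-level analogue on class proportions.

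**Section 2.3.** State the assumed class size, number of classes and ICC of change. Restate the detectable effect or power for the 144 children instead of enrolling more.

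**Cost.** The change is to wording and analysis; the class and school of each child are known. The price is wider intervals and few degrees of freedom. With three school pairs, the class-level comparison has 2 degrees of freedom and a critical t of 4.30 in place of 1.96. Assuming 20 per class, its power for a difference of 0.52 SD is about 32%, 22% and 17% at ICC 0.01, 0.05 and 0.10. That is what the design can support, and the child-level test conceals it. If there is only one class per arm, no model can separate class from arm, and the between-arm p-value should be reported as descriptive. Neither analysis removes the confounding of arm with school year, which the Discussion already acknowledges.

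### Repeated-measures ANOVA and Cochran's Q, read over three waves, drop a child who misses only the one-month questionnaire from the pre-post comparison too; this costs precision and can bias that comparison

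*Protocol article*

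**What the plan says.** Section 2.8 (Statistical Analysis) names a test for each type of response.

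- Quantitative: "Quantitative variables will be analysed using an ANOVA of repeated measures test using the group as a factor of the independent level (parametric"). The non-parametric alternative is Wilcoxon's test within each group.
- Two categories: "qualitative variables in two categories will be analysed with Chi-square and Cochran"'s Q.
- More than two categories: "qualitative variables in more than two categories will be analysed with Chi-square and McNemar Bowker"'s test.

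The same section reports "data from the pre-, post- and retention test (one month after) questionnaires will be reported per group", so there are three waves. Sections 2.5.2 and 2.6.1 place the third wave one month after the intervention and count all three measurements under the primary outcomes.

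On loss of participants, section 2.3 says: "Based in the dropout of similar studies [35,36,37], the final sample size will be increased by 20% to reach 144 children". The article does not say how an incomplete record enters the tests. On software, section 2.8 says: "Data will be entered and analysed using SPSS 28.0 software".

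**The concern.** Classical repeated-measures ANOVA and Cochran's Q both work on complete rows. Section 2.8 does not say outright that all three waves enter one test, but that is the natural reading. With two waves Cochran's Q reduces to McNemar's test, so naming it points to three.

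On that reading, a child with valid pre and post answers and no one-month answer contributes nothing, even to the pre-post contrast. In the intervention group each topic's pre and post parts are completed at the start and end of the same session, with the research team present. The one-month questionnaire comes later, with schoolteachers helping. Loss at the last wave alone is therefore plausible, and the children deleted would often hold complete pre-post pairs.

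Two things are at stake: precision that has already been collected, and possible selection if the children who return differ from those who do not, in a way that differs between arms. Items from one questionnaire would also rest on different sets of children according to response format, since Wilcoxon and McNemar-Bowker use pairs of waves.

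**Working it through.** **Inputs from the protocol.** Base size 120 for attitude and 60 for knowledge, 80% power, alpha 5%, increase of 20% to 144 (2.3); three waves (2.8); groups of similar size (2.5.2). **Assumed, because not given:** two-sided test, correlation 0.5 between any two waves, all loss at one month, three waves in both arms.

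**1. The plan's own figure.** 120 × 1.20 = 144, which reproduces. It covers a loss of 1 − 120/144 = 16.7% in full. Keeping 120 complete cases at a 20% loss would need 120/0.80 = 150.

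**2. Power against the plan.** At a 20% loss, 144 × 0.80 = 115 complete cases. If 120 gives 80% power, 115 gives Φ((1.960 + 0.842) × √(115/120) − 1.960) = Φ(0.783) = 78.3%. A noncentral F calculation for the group-by-wave interaction gives 78.2%. For knowledge, 115 is still well above 60.

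**3. Precision against the data collected.** If a fraction m misses only the last wave, complete-case analysis inflates the pre-post standard error by √(1/(1 − m)).

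- m = 16.7%: √(144/120) = 1.095
- m = 20%: √(1/0.80) = 1.118

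With 72 per group and correlation 0.5, the change score has variance 2(1 − 0.5) = 1 SD². The standard error of the group difference is then √(2/72) = 0.167 on all pairs and √(2/57.6) = 0.186 on complete cases. A simulation of 4,000 trials with about 20% missing at one month gave:

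| Contrast | SE, complete cases | SE, all available | Ratio |
|---|---|---|---|
| Pre-post | 0.185 | 0.166 | 1.11 |
| Pre to one month | 0.184 | 0.178 | 1.03 |

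**4. Bias.** Same simulation, true pre-post difference 0.50 SD. Low post scorers in the intervention group only are made more likely to miss the last wave.

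| Log-odds of absence per SD (assumed) | Pre-post, complete cases | Pre-post, all available |
|---|---|---|
| 0 (chance only) | 0.504 | 0.503 |
| 0.5 | 0.549 | 0.499 |
| 1.0 | 0.604 | 0.501 |

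In the two selective scenarios the complete-case pre to one-month difference stayed at 0.498 and 0.497. With equal correlations between waves, that change is unrelated to the post score. The bias shown here is therefore confined to the pre-post contrast.

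**The case against.** **The plan already allows for dropout.** This stands for planned power. A reader might infer that the plan expects 20% dropout and that power therefore falls from 80% to 71%, from Φ(2.802/1.118 − 1.960) = 0.71. The documents do not support that. Section 2.3 raises N by 20% and states no dropout rate, and 144 is already the enlarged number. The 71% holds only for a comparison that would have 80% power on all collected pre-post pairs, with every loss at one month. The enlargement does not, however, remove selection.

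**Missing-data handling may sit in an analysis plan that is not shown.** This stands as far as silence goes: nothing in the article excludes imputation. The point is about the tests that section 2.8 does name.

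**The scenario favours the point.** This stands in part. A child in the intervention group who is absent from a session loses that topic's pre and post parts together, and no model recovers that change. The timing of loss is not given. Section 2.5.2 also does not make clear that controls are measured three times, as the count of 115 assumes.

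**The scope is narrow.** This stands. Wilcoxon by group and McNemar-Bowker use pairs of waves, and chi-square can compare groups at each wave. Many questionnaire items are open or categorical.

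**The bias is speculative.** Its size is assumed. Nothing in the documents shows that absent children are less engaged, and absence that depends on baseline alike in both arms need not bias the group difference in change. That it can arise under selective absence differing by arm stands.

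**Conclusion.** The point holds in a limited form. On the three-wave reading, the two named tests leave out collected pre-post data from children who miss only the one-month questionnaire. Power against the planned 120 falls by about 2 points at a 20% loss and not at all at 16.7%, so this is not an underpowered trial on this account.

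The cost is a pre-post standard error about 10 to 12% larger than the data allow if losses fall at one month, and about 3% for pre versus one month at correlation 0.5. There is also exposure to bias if absence depends on observed scores differently by arm. The reading of 0.55 to 0.60 for a true 0.50 SD illustrates that mechanism under assumed dropout and does not forecast this trial. A reader might infer that the result will be biased or that every outcome is affected; the documents support neither.

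The change is worth making because the alternative is cheap and needs a weaker assumption about why data are missing.

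**What to change.** In section 2.8:

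- Replace repeated-measures ANOVA by a linear mixed model on all available observations, with arm, wave, and arm by wave as fixed effects and an unstructured covariance over waves. Keep any class or school term that the cluster design needs.
- Replace Cochran's Q by a likelihood-based logistic mixed model with the same terms. Unweighted GEE is not a substitute: it generally needs data missing completely at random, so the weaker assumption that motivates the change would be lost.
- Keep the complete-case analysis as a sensitivity analysis, and report the number of children contributing at each wave by arm.

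The cost is a few sentences and slightly more analysis work. No new data are needed, and SPSS 28.0, already named, fits both models.

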The next step will be to implement and measure the effectiveness of the intervention proposed here. This step will be taken in the near future. It is important to highlight that the effectiveness of the intervention will be assessed by monitoring the participants using a questionnaire one month later. This approach takes into consideration the findings of previous studies that emphasise the significance of evaluating the long-term results. It is crucial to ensure that the acquired knowledge and behaviour can be sustained over time, thus providing a more comprehensive understanding of the intervention’s impact [77,78,79].

In this sense, it should be noted that this study has some weaknesses. It is a non-randomised trial; thus, some bias is expected. In addition, the control group attends a higher level at the same school than the intervention group, so there could be differences in knowledge and attitudes due to age. However, it has been considered that the control group would be even more different by choosing control groups of the same age but from different schools, since socio-cultural differences by territory (and consequently, by school) are an important aspect to take into account. At the same time, this weakness could be considered a kind of strength, because most interventions at schools do not consider any control group at all [80]. It is also remarkable that the design of Zeliakide is practical and suited to the reality of schools, and so it is easily applicable to other centres in the future. 

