The student should be able to understand the work of scientists, to know that the gluten content of foods is analysed through experimentation.	*Bloom level 6. Evaluation* The student is able to perform experimental work, observe, analyse and evaluate the results.	All the experiments.	Day 4. What gluten is Day 5. Differences between gluten and gluten free foods Day 6. Food labels Day 7. Where gluten is
The student should be able to assess the impact of own actions on others.	*Bloom level 6. Evaluation* The student demonstrates empathetic behaviour. The student selects actions and behaviours to overcome differences between people.	Game to learn the characteristics of the disease. Case study to work on inclusion: discussion.	Day 8. Social inclusion of people with celiac disease Day 3. Celiac Disease (transversally) Day 5. Differences between gluten and gluten free foods (transversally)

Meaning of “transversally”: some activities or days, in addition to developing their specific competencies and learning outcomes, contribute in a transversal way in the achievement of others. Thus, “transversal” has been used to indicate this situation.

**Table 2 nutrients-16-00338-t002:** Zeliakide intervention study schedule.

Intervention Group				Control Group
**Week**	**Topic Session 1**	**Topic Session 2**	**Challenge**	No intervention
1	Day 1. Food groups	Day 2. Healthy diet	“Healthy snacks challenge”	
2	Day 3. Celiac Disease	Day 4. What gluten is		
3	Day 5. Differences between gluten containing and gluten free foods	Day 6. Food labels		
4	Day 7. Where gluten is	Day 8. Social inclusion of people with celiac disease		

**Table 3 nutrients-16-00338-t003:** Competency-based intervention: outcome measures.

Competence	Outcome Measures
The student should be able to place the food groups in the food pyramid.	Change in nutrition knowledge
The student should be able to identify dietary errors and make recommendations for modification.	Change in nutrition knowledge
The student should be able to consume less food from the top of the pyramid.	Change in behaviour in relation to the consumption of unhealthy foods
The student should be able to explain what celiac disease is.	Change in Celiac Disease knowledge
The student is able to assess the impact of their own actions on others.	Change in intentional behaviour related to the social inclusion of people with celiac condition: perception of the influence of one’s own actions on others.

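### Only the parametric route compares change between arms; the tests named for skewed and categorical outcomes do not estimate the between-arm difference in change

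*Protocol article*

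**What the plan says.** Section 2.8 states the purpose first: "For the analysis of the differences between groups, a variety of statistical tests will be used depending on the type of response to the questions". It then assigns tests by type of variable.

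- Quantitative, parametric: "ANOVA of repeated measures test using the group as a factor of the independent level (parametric".
- Quantitative, non-parametric: "Wilcoxon’s test segmenting by group (non-parametric".
- Two categories: "qualitative variables in two categories will be analysed with Chi-square and Cochran’s Q tests".
- More than two categories: "qualitative variables in more than two categories will be analysed with Chi-square and McNemar Bowker’s tests".

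Section 2.1 describes a "two-armed cluster, non-randomised and controlled trial, conducted among 10–12-year-old children with a pre- and post-intervention evaluation and 1 month follow-up". Table 3 words every primary outcome as a change, for example "Change in behaviour in relation to the consumption of unhealthy foods". Section 2.4 takes controls from the school year above, in the same school. The Discussion accepts that "there could be differences in knowledge and attitudes due to age".

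**The concern.** A controlled trial whose outcomes are changes has one natural target: how much more the intervention arm changed than the control arm. The ANOVA route can deliver that through its group-by-time term. The other routes, as named, offer either change inside one arm or a comparison of arms with no stated use of baseline.

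Two errors then become possible. A significant change in the intervention arm beside a non-significant one in the control arm may be taken as evidence of an effect, although the two changes were never compared. Alternatively, a post-test comparison may be taken as the effect, although it includes whatever gap existed between the two grades at the start.

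**Working it through.** The point concerns method, and no figure in the article decides it. The check classifies each named test and then sizes the two possible misreadings.

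**Step 1. What each named test compares**

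| Route in section 2.8 | Test | Between arms? | Uses baseline? |
|---|---|---|---|
| Quantitative, parametric | Repeated-measures ANOVA with group as factor | Yes | Yes, through group × time |
| Quantitative, non-parametric | Wilcoxon, segmented by group | No | Yes, inside one arm |
| Two categories | Chi-square | Yes | Not stated |
| Two categories | Cochran's Q | No | Yes, inside one arm |
| More than two categories | Chi-square | Yes | Not stated |
| More than two categories | McNemar-Bowker | No | Yes, inside one arm |

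Below the first row, no test is stated to do both.

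**Step 2. Arm sizes used**

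Section 2.3 gives 120 children for attitude, raised by 20%: 120 × 1.2 = 144. Section 2.5.2 makes the arms of similar size, so 120/2 = 60 per arm before the increase and 144/2 = 72 after it. The 60 children given for knowledge would be 30 per arm.

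**Step 3. If effectiveness were read from separate within-arm tests**

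Assume the same true change in both arms, for example from retesting. If each arm's test is significant with probability p, the chance that only the intervention arm is significant is p(1 − p), which is at most 0.25.

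Simulation with signed-rank Wilcoxon in each arm, 60 per arm, 2,000 trials per setting, counting only positive intervention results:

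| Equal change (SD of change) | Intervention significant, control not |
|---|---|
| 0 | 2.15% |
| 0.15 | 16.0% |
| 0.20 | 21.6% |
| 0.25 | 24.7% |
| 0.30 | 25.5% |
| 0.35 | 18.4% |

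The excess over 25% at 0.30 is simulation error. A separate run of 4,000 trials per setting, counting either direction, gave intervention-only significance in 14% to 26% over 30 to 72 per arm and equal changes of 0.20 to 0.32 SD. At 60 per arm and 0.25 SD it found arm-wise significance of 0.4665 and 0.46225. The formula then gives 0.4665 × (1 − 0.46225) = 0.251, against 25.7% simulated. In the same run a Mann-Whitney test between arms on the change scores rejected in 4.4% to 5.6% of trials in every setting with equal change.

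**Step 4. If effectiveness were read from a post-test Chi-square**

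Assume 40% correct at baseline in the intervention arm and a gain of 15 points in both arms, so the true difference in change is zero.

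| Baseline lead of controls | Significant, 60 per arm | Significant, 72 per arm |
|---|---|---|
| 0 points | 5% | 5% |
| 10 points | 21% | 24% |
| 20 points | 64% | 71% |

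A gap can also hide an effect. Assume the intervention arm goes from 45% to 65% and controls stay at 60%. The difference in change is (65 − 45) − (60 − 60) = 20 points, but the post-test difference is 65 − 60 = 5 points. With 60 per arm, SE = √[(0.65 × 0.35 + 0.60 × 0.40)/60] = 0.088 and 0.05/0.088 = 0.57, so two-sided power is about 9%.

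**Step 5. How many outcomes are affected**

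Table A1 has 32 question rows: 7 numeric scales, 11 closed categorical questions, 2 food lists that could be scored as counts, and 12 open questions. Table 3 sets outcomes by competence, and the rule for combining rows into outcomes is not shown. The number of outcomes on each route cannot be derived.

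**The case against.** Several objections limit the point.

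- **Chi-square does compare arms.** The article does not say at which time point it is applied, and it could be run on categories of change. This stands as a caution. Nothing in the text says so, however, and its pairing with paired tests over time suggests a cross-sectional comparison. A reader might infer that the control arm adds nothing on these routes; that goes too far.
- **The ANOVA route may carry much of the evidence.** Section 2.3 plans on Cohen's d, and the Discussion speaks of about one point on a 0–4 scale, so a quantitative knowledge score may be intended. A reader might infer from Table A1 that most primary outcomes bypass the ANOVA; without the scoring rule that is an assumption.
- **No decision rule is stated.** The article never says that significance in one arm only will count as success. The 16–25% is therefore conditional on that rule and on an equal change chosen for illustration. It is not this trial's false-positive rate, and it speaks only to Wilcoxon.
- **Two-wave tests are not wrong in themselves.** Wilcoxon and McNemar-Bowker can be run on pairs of the three waves.
- **Detail may sit in a fuller document.** That would answer an omission. Here the article names the tests, and they do not match the purpose it gives them.

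**Conclusion.** The point holds for outcomes that take the non-parametric or categorical routes: no test named for them is stated to estimate the between-arm difference in change that Table 3 makes primary. It does not hold for the parametric route, and the documents do not show what share of outcomes is affected.

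The classification of tests in Step 1 needs no assumption beyond reading Chi-square as listed. The sizes do. The figure of about 16–25%, against about 2% with no change, rests on an unstated decision rule, 60 per arm and an equal true change of 0.15 to 0.35 SD. The Chi-square figures rest on assumed baseline gaps and response rates. The article's own expectation of differences due to age makes a baseline gap plausible but does not size it.

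**What to change.** In section 2.8, name a between-arm comparison of change (group × time) as the effectiveness test for each primary outcome measured at baseline in both arms.

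- Suitable forms are a logistic or ordinal mixed model, a GEE, or a between-arm rank test on change scores stratified by school.
- Allow for clustering by class or school, with a small-cluster correction where clusters are few.
- Report each effect with its 95% confidence interval.
- State that the contrast removes stable differences between grades only if both grades would otherwise have changed in parallel. Arm and grade coincide, so the data cannot separate them.
- Keep Wilcoxon, Cochran's Q and McNemar-Bowker as within-arm description.
- Report descriptively the Table A1 items with no meaningful baseline, such as the one asking whether the sessions taught the child enough to improve their diet.

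The cost is slightly more modelling. The fix uses the pre, post and retention data that section 2.8 says will be reported for both groups. Section 2.5.2 describes the control questionnaire as filled in at one session during the intervention month, so the text should confirm that controls complete each wave.
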